## Analysis

### Statistical analysis

Analyses will be conducted using STATA 13 [60]. Descriptive statistics will be used to summarise clinical and demographic characteristics of patients. Feasibility of trial procedures will be examined using proportions and 95% confidence intervals for assessments of feasibility and acceptability in terms of recruitment, consent, dropout, follow-up and integrity of double blinding.

The variance observed in this sample will be used for sample size calculation for the future RCT. As recommended by Browne [37] and Lancaster and colleagues [39] the 80% upper one-sided confidence limit of the variance estimate rather than the variance estimate itself will be used. The final effect size for sample size calculations will be obtained by dividing the minimum clinically important difference by this variance estimate. We define a clinically important difference as a symptom score drop of ≥20%. To assess efficacy of the intervention using the *SRT* [41] a three-factorial within-and-between group design will be used with a random-effects model [61]. These analyses will follow the intention-to-treat principle, with data from all participants who entered the study included into the analysis. Emphasis will be on confidence interval of effect sizes estimation rather than hypothesis testing which allows us to assess the imprecision of the estimates. Rates and characteristics of dropout will be explored and where appropriate, statistical techniques for handling missing data will be used. Furthermore, to address a limitation given the size of the sample employed, statistical analyses will be corrected for multiple testing.

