### Feasibility, double-blind randomised controlled trial

The current study is a feasibility, double-blind RCT of CBM-pa with patients who suffer from persistent, distressing paranoid symptoms. The CBM-pa intervention is delivered on a computer, set up by the researchers and, thereafter, is a self-directed, automated package, self-administered by the patient. The intervention uses ambiguous scenarios which could potentially be interpreted in a manner that reinforces paranoia, or instead could be interpreted in more benign way. While patients read these scenarios they are asked to complete experimental tasks (word completion and comprehension questions) which implicitly influence the interpretation that is actually made. Additional file 1: Figures S1a–h shows an example trial from the intervention. The intervention aims to reduce paranoid beliefs, paranoid symptoms and stress/distress, and will be evaluated in comparison to a text-reading control (see Additional file 1: Figure S1i). Both conditions will be conducted in addition to Treatment as Usual (TAU) which will be in the form of individualised combinations of medication and care coordination. This design directly evaluates the hypothesised ‘active ingredient’ (bias reduction) by using the control condition to match all other aspects of the adjunct intervention.

The main objective of this feasibility study is to test the integrity of the protocol in terms of length and feasibility. A secondary objective is a preliminary evaluation of efficacy. For this the primary outcome is the severity of paranoid symptoms. A third objective is the selection of primary outcomes (e.g. paranoid symptoms, interpretation bias and vulnerability to stress) for the subsequent trial based on consensus after presentation of results to the Steering Group. This decision will be informed by (1) observed effect sizes and (2) opinions on the most important outcome from qualitative interviews. The necessary withholding of information about group assignment might be a significant issue because heightened suspiciousness is an inherent feature of clinical paranoia.

Estimates of population variances of the main outcomes for future power calculations will be based on Browne [37], who suggests using the upper 80th percentile of confidence intervals around the estimates.

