### Secondary outcomes

The study will sample three domains of possible outcomes: interpretation bias, clinical symptoms and stress/distress. For each we will collect information on (1) comprehensibility and suitability and (2) variance estimates by calculating standardised treatment effect sizes (Cohen’s *d*) and their confidence intervals.

Interpretation bias will be measured using the:
*Similarity Rating Task (SRT)* [41]. This is a standard test used to measure interpretation bias. Items describe ambiguous social scenarios that permit either paranoid- or non-paranoid interpretations and were developed by Savulich et al. [17], based on Freeman and Garety’s [46] definition of paranoia as a person’s belief that intentional ‘harm is occurring, or is going to occur’. Items are shown to have sensitivity to detect differences between high-paranoid and low-paranoid groups of participants who were found to differ in their interpretation bias on paranoid item content [17], such that the high-paranoid group showed a significantly more maladaptive pattern of interpretation (reduced endorsement of positive and non-paranoid interpretations) compared with the low-paranoid group

For the ‘encoding’ part of the task participants read 12 ambiguous passages, complete one of the last word’s missing letters and answer a comprehension question. An example of such a passage is entitled ‘car park’, followed by ‘You have parked your car in the supermarket car park and just done your weekly food shopping. On your return to your car you notice a man sat in a nearby car. He is sitting alone and looking out the w-nd-w.’ Hence, for each item, the third sentence ends with a word that has several letters missing. Participants are asked to indicate the first missing letter. For the ‘Car park’ example, the letter ‘i’ would have to be indicated to show that the last word was ‘window’. In order to check that participants correctly encoded the passage, they had to choose ‘yes’ or ‘no’ as an answer to a comprehension question, such as ‘Have you just been to the supermarket?’ which would be correctly answered with ‘yes’ in the ‘Car park’ example. Participants are given feedback on the screen about the correctness of their response to this comprehension question.

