Psychotic symptoms are measured at baseline using the *PANSS* [40] conducted by a trained clinical psychologist. This is a 30-item clinical tool that measures symptom severity in psychosis. It consists of three subscales with seven items for positive symptoms, seven items for negative symptoms and 16 items for general symptoms. Each symptom is rated on a 7- point Likert scale from 1 (symptom absent) to 7 (symptom extreme), with a minimum score of 7 and a maximum score of 40 for the *PANSS* subscales; and a minimum score of 16 and a maximum score of 112 for the general symptoms.

Specifically, severity of paranoid symptoms is assessed by *PANSS* item 6 (P6 Suspiciousness/Persecution) which can be used in isolation to evaluate degree of clinical paranoia. This item measures unrealistic or exaggerated ideas of persecution using a 7-point Likert scale where 1 = absent; 2 = minimal, may be at upper extreme of normal limits; 3 = mildly symptomatic, then incrementally upwards to 7 = extreme persecutory delusions.

In addition to the *PANSS* item 6, the following self-report scales will be used to assess paranoid symptoms: the *Paranoia Scale* [50], the *Paranoid Thoughts Scale* [51] and the *Peters Delusions Inventory* (*PDI-21*) [52]. Although the latter is not a clinical symptom measure, it includes subscales reflecting clinically important elements of delusional ideation: degree of delusional conviction, frequency of delusional thoughts and degree of associated distress.

Symptoms of depression/anxiety are assessed using the *Hospital Anxiety and Depression Scale (HADS)* [53].

Stress/distress is assessed using three measures:

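### The effect size for planning the next trial is defined as the clinically important difference divided by a variance limit, where a standard deviation is needed

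*Protocol article*

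**What the plan says.** Three statements in the Statistical analysis section form a chain.

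- Purpose: "The variance observed in this sample will be used for sample size calculation for the future RCT".
- Which estimate: "the 80% upper one-sided confidence limit of the variance estimate rather than the variance estimate itself will be used".
- The formula: "The final effect size for sample size calculations will be obtained by dividing the minimum clinically important difference by this variance estimate".

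In the third statement, the estimate referred to can only be the variance limit named in the second. The numerator follows directly: "We define a clinically important difference as a symptom score drop of ≥20" per cent. It names no scale and gives no value in points.

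Under Secondary outcomes, the same article names Cohen's d as its standardised effect measure for each outcome domain. The text at hand mentions neither a standard deviation nor a square root anywhere; the Background and the Participants and study setting section also speak only of variances.

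**The concern.** Cohen's d is a difference in points divided by a standard deviation in points, so it has no units and can go straight into a sample-size formula. A difference divided by a variance has units of one over points. It changes when the same scale is re-expressed, although nothing about the patients or the treatment has changed. The formula therefore disagrees with the article's own effect measure.

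At stake is the size of the definitive trial. Obtaining variances for that calculation is a declared purpose of this pilot. Someone who follows the rule literally would get a required number that is wrong by a factor set by the scale. An absurdly large number would probably be noticed. A moderately wrong one on a narrow scale such as PANSS item 6 might not be, and where the variance is below 1 the next trial would be underpowered.

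**Working it through.** **The plan's own figure.** The only reproducible sample-size figure is the precision of the follow-up rate in Participants and study setting: 60 patients, 70% followed up, one-sided 95% interval. 1.645 × √(0.7 × 0.3 / 60) = 0.097, which agrees with the stated limit of 10%. It does not use the effect-size rule. No number, standard deviation, significance level or power is stated for the future trial, so the rest uses declared assumptions.

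**The general factor.** For two equal arms compared on a mean, n per arm = 2(z₁ + z₂)² / d², where z₁ and z₂ are the normal quantiles for the significance level and the power. Let V be the upper-limit variance and Δ the important difference.

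- Correct: d = Δ/√V, so n = 2(z₁ + z₂)² V / Δ².
- As written: d = Δ/V, so n = 2(z₁ + z₂)² V² / Δ².
- Ratio, as written to correct: V, whatever the significance level, power or Δ.

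**Units.** Take Δ = 0.8 and SD 1.2. The correct effect size is 0.8/1.2 = 0.667 and the written one is 0.8/1.44 = 0.556. Multiply every score by 10: the correct value is 8/12 = 0.667 again, but the written one is 8/144 = 0.0556.

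**Illustration on PANSS item 6**, which is scored "using a 7-point Likert scale where 1 = absent". Assumptions:

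- Mean 4, so a 20% drop is Δ = 0.8 points.
- Two-sided 5% and 90% power, so 2(1.960 + 1.282)² = 21.01.
- 42 patients with data (70% of 60), hence 40 degrees of freedom after two arm means. The 80% upper-limit factor is 40 / 32.35 = 1.237, where 32.35 is the 20th percentile of chi-square on 40 df.

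Then n correct = 21.01 × V / 0.64 = 32.84 × V, and n as written = 32.84 × V².

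| Assumed SD | V = 1.237 × SD² | n per arm, correct | n per arm, as written |
|---|---|---|---|
| 0.7 | 0.606 | 19.9 → 20 | 12.1 → 13 |
| 0.9 | 1.002 | 32.9 → 33 | 32.9 → 33 |
| 1.0 | 1.237 | 40.6 → 41 | 50.2 → 51 |
| 1.2 | 1.781 | 58.5 → 59 | 104.1 → 105 |

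The two rules agree where V = 1, that is at a sample SD of 1/√1.237 = 0.90. Above that the written rule oversizes the trial; below it, it undersizes the trial.

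**Other assumed scales** (80% power, SD taken as already at its upper limit):

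- Δ = 0.5, SD 0.8: 41 per arm correct, 26 as written. With 26 per arm the true power is 0.615 instead of 0.80.
- Δ = 10, SD 15: 36 per arm correct, 7,947 as written. The factor before rounding is 15² = 225.

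**The case against.** The strongest reply is that the sentence is loosely worded. Cohen's d is named elsewhere, any statistician planning the next trial would take the square root, and the variance and its upper limit are themselves specified sensibly. Loose wording is possible, but nothing in the text says so: the formula is explicit and every related sentence speaks of variances. The reply limits the damage without making the rule correct.

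It is also fair that feasibility is the main objective, that the primary outcomes are rates of recruitment, consent, dropout and follow-up, and that 60 patients are justified first by pilot convention and the precision of the follow-up rate. The variance argument for at least 30 patients does not depend on the division. All of this stands and bounds the point.

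A reader might infer more than the document supports:

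- **That a sample size is already wrong, or that the pilot exists mainly to supply one.** No future number is printed, and variance estimation is one purpose among several.
- **That the 20% is a within-patient, raw-score change.** The text does not say so. Subtracting the scale minimum on item 6 first is a convention, not a correction.
- **That the 20% rule breaks down on the signed Similarity Rating Task score, or gives enormous numbers on the Scrambled Sentences Task.** The 20% is defined for a symptom score, and both tasks belong to the separate interpretation-bias domain. The choice of primary outcome for the next trial is deferred.
- **That no variance can come from "variance estimates by calculating standardised treatment effect sizes".** The phrase is awkward, but computing Cohen's d requires each outcome's standard deviation, so nothing is lost.

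**Conclusion.** The point holds as an error in a prescribed formula. The factor V is exact for the usual comparison of two means. Its size and direction depend on the outcome: on PANSS item 6, under the stated assumptions, it runs from an undersized trial at SD 0.7, through no practical difference at SD 0.9, to about 1.8 times the correct number at SD 1.2. Symptom scales with a wider score range would see far larger inflation. The means, standard deviations, power, significance level and completer count behind these figures are assumptions; the document gives none of them for the future trial.

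Nothing in this trial's allocation, data collection or feasibility estimates is affected. The consequence arises only when the rule is applied as written to plan the next trial.

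**What to change.** Replace the sentence with a rule of this form: planning effect size = minimum clinically important difference, in points on the chosen scale, ÷ √(80% upper one-sided confidence limit of the pooled within-arm variance).

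This keeps the intended conservative allowance for uncertainty in the variance, removes the dependence on units, and agrees with the Cohen's d named under Secondary outcomes. It costs one sentence in the protocol or analysis plan and needs no new data and no change to trial conduct.

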At week 6, after receiving the intervention, the assessment (T_1_) includes measures of:Paranoid beliefs (*SRT*, *SST* and *CFS*). As for T_0_, *SRT* and *SST* contain the same number of items (12 and 15, respectively) and are counterbalanced across participantsClinical symptoms (*PANSS* item 6, *Paranoia Scale*, *Paranoid Thoughts Scale*, *PDI-21* and *HADS*)Vulnerability to stress using the *Laughter Task* and *VRE* in counterbalanced order

Participants will be contacted at 1 and 3 months from end of the session 6 for follow-up assessments (T_2_–T_3_) which include:Paranoid beliefs measured, using a total of 12 items from the *SRT*
Clinical symptoms (*PANSS* item 6, *Paranoia Scale*, *Paranoid Thoughts Scale*, *PDI-21* and *HADS*).

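### The 20% score drop that sets the next trial's effect size ignores the floor of 1 on PANSS item 6, does not separate change from baseline from a between-arm difference, and cannot serve the SRT

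*Protocol article*

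**What the plan says.** The Statistical analysis section sets the threshold: "We define a clinically important difference as a symptom score drop of ≥20" per cent. It then gives the use: "The final effect size for sample size calculations will be obtained by dividing the minimum clinically important difference by this variance estimate". The denominator is conservative, since "the 80% upper one-sided confidence limit of the variance estimate rather than the variance estimate itself will be used". Nothing says which symptom scale is meant, whether the scale minimum is first subtracted, or whether the 20% applies to a patient, a group mean or a contrast between arms.

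The Secondary outcomes section describes PANSS item 6 as a 7-point scale "where 1 = absent; 2 = minimal, may be at upper extreme of normal limits; 3 = mildly symptomatic", rising to 7. Participants and study setting requires a score of at least 3 for entry. The background section on the feasibility trial makes severity of paranoid symptoms the primary outcome for the preliminary efficacy evaluation. It also plans the "selection of primary outcomes (e.g. paranoid symptoms, interpretation bias and vulnerability to stress) for the subsequent trial".

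The SRT bias score runs from −3 to +3, positive values are the benign direction, and the screening cutoff is 1 or below. Among the week 6 (T1) measures, Procedures lists "Vulnerability to stress using the *Laughter Task* and *VRE* in counterbalanced order". The T0, T2 and T3 lists contain neither task.

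**The concern.** A percentage of a score is interpretable only if zero on the scale means none of the thing measured. On PANSS item 6, none is scored 1. A percentage of the raw score therefore treats the floor as illness and sets a larger target difference than the same percentage of actual severity. A larger numerator gives a larger effect size and a smaller trial.

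Supplying inputs for the next trial's sample size is a declared purpose of this pilot. The upper confidence limit on the variance is chosen so that the next trial is not planned too small. An inflated numerator works against that protection.

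Two further gaps follow from the same sentence. A drop describes change over time, whereas a two-arm sample size needs a difference between arms. In addition, two of the candidate domains for the next primary outcome are not symptom scores, and the section gives no other threshold for them.

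**Working it through.** **The plan's own figure.** The only computed design figure is the precision of the follow-up rate. With 70% and n = 60, 1.645 × √(0.7 × 0.3 / 60) = 0.097, which agrees with the stated limit of 10%. It does not use the 20% rule, so the target of 60 stands.

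**PANSS item 6.** The inputs are a scale of 1 to 7 with 1 = absent, entry at 3 or more, and a 20% threshold. For mean baseline b, the raw reading gives 0.20 × b and the floor-removed reading gives 0.20 × (b − 1). Required N is proportional to 1/difference² for a fixed SD, so the floor-removed N divided by the raw N is (b / (b − 1))².

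| Mean baseline b | Raw 0.20b | Floor removed 0.20(b − 1) | Raw difference as share of severity above absent | N ratio |
|---|---|---|---|---|
| 3 | 0.6 | 0.4 | 0.6/2 = 30% | (3/2)² = 2.25 |
| 4 | 0.8 | 0.6 | 0.8/3 = 27% | (4/3)² = 1.78 |
| 5 | 1.0 | 0.8 | 1.0/4 = 25% | (5/4)² = 1.56 |

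The ratio depends only on b. It holds for any denominator that is the same under both readings, so it is separate from the question of dividing by a variance or an SD.

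**In patients per arm (illustration).** The documents give no SD, so I assume 1.0 to 1.5, with two-sided alpha 0.05, 80% power and n per arm = 2 × (1.960 + 0.842)² × SD² / difference².

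| Mean baseline | SD 1.0: raw / floor removed | SD 1.5: raw / floor removed |
|---|---|---|
| 3 | 44 / 99 | 99 / 221 |
| 4 | 25 / 44 | 56 / 99 |
| 5 | 16 / 25 | 36 / 56 |

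**SRT.** Improvement is a rise, and the screening cutoff allows baselines on both sides of zero. Multiplying by 0.8 takes +1 to +0.8 (worse), leaves 0 at 0, and takes −1 to −0.8 (better). One rule therefore means harm, nothing or benefit, depending on the starting value.

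**Laughter Task and VRE.** The text lists them at T1 only, so there is no earlier score to drop from. The Laughter Task responses are rated for presence of a paranoid attribution, for which a proportion is the natural summary.

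**SST and VAS mood.** The SST score runs from 0 to 100, higher is worse, and it is taken at T0 and T1; 60 to 48 is a valid 20% drop. VAS mood is recorded before and after each training session, so a percentage change can be calculated there too.

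**Drop against difference.** If the active arm falls by D and the control arm by C, the between-arm difference is D − C. It equals the drop only if C = 0. The section does not say which quantity the 20% refers to.

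**The case against.** The best reply is that the rule says symptom score, and the article treats symptoms, interpretation bias and stress/distress as separate domains. On that reading, it was never meant for the SRT, the Laughter Task or the VRE. That is fair, and it narrows this limb: the rule cannot be carried over to those measures, and no other threshold is stated for them.

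A reader might infer that the rule cannot be computed for two of the three candidate domains. The documents do not support that, because the SST and VAS mood allow a percentage change. VRE scores could also be compared with the control mean.

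A reader might also argue from single patients: a one-point fall meets 20% at scores 3 to 5, but two points are needed at 6 and 7. That requires a patient-level reading which the section does not state. Its use as an effect-size numerator points more towards a group mean, which need not move in whole points. For the same reason, it cannot be asserted that the plan mistakes a responder threshold for a planning difference; it simply does not say which is meant.

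Comparing a mean baseline of 3 with one of 5 on the raw scale gives (1.0/0.6)² = 2.78. However, a relative criterion is meant to vary with baseline, so that contrast does not measure an error. The floor ratio at a given mean does.

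It is also true that item 6 is one of several paranoia measures and is not named as the scale for this rule. Nothing in the present trial is sized by the rule. Both points limit the consequence, but they do not remove it: the article states the rule and its use, and item 6 is its measure of paranoia severity.

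**Conclusion.** The concern holds in this limited form. Applied to raw PANSS item 6 scores, the stated rule overstates a 20% reduction in severity. For the same SD, the next trial would be too small by a factor of 2.25, 1.78 or 1.56 at mean baselines of 3, 4 and 5. A mean of 3 is the lower extreme, given entry at 3 or more, so 2.25 is close to the upper end.

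This assumes that item 6 is used for planning, that 20% is taken of the group mean, and that the intended meaning is 20% of the severity above absent. If the raw-score reading was deliberate, the remaining fault is that it is unstated. The per-arm numbers also rest on assumed SDs.

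The rule has no coherent meaning on the SRT and, as change from baseline, does not fit the Laughter Task or VRE. The absence of a baseline for those two tasks rests on the text, since the SPIRIT figure is not shown. The consequence falls on the future trial.

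**What to change.** Before unblinding, state for each candidate primary outcome a between-arm difference in points, or in proportions for the Laughter Task, together with the direction of improvement. For the SRT, give points on the −3 to +3 scale with a rise as improvement. For the VRE, use a difference in T1 scores. The difference need not be a whole point, on item 6 or elsewhere. If a percentage is kept for symptom scales, name the scale, subtract its minimum first, and say that the percentage is taken of the group mean.

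The cost is a change of protocol wording and a Steering Group discussion to justify each difference, which is real work for several instruments. The future sample size on item 6 will come out larger. No new data are needed.

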A typical item is shown in Additional file 1: Figure S1b. Each item depicts an emotionally ambiguous situation, is interactive and involves participants reading three lines of text on a computer screen, then completing a missing word and answering a related question (yes/no). Both the word completion and the question encourage participants to interpret the ambiguity inherent in the situation in a manner that promotes helpful beliefs about themselves and others (see example given in Additional file 1: Figures S1a − h). Equal numbers of ‘yes’ and ‘no’ question responses are presented randomly to avoid participants developing a fixed response set. Word completions were unique (no repetitions) and constructed by removing all vowels, then reinstating one in cases where LEAP feedback indicated that the resulting difficulty level was too high. In response to further feedback from LEAP a ‘clue’ was created for each item by adding more letters to encourage the participant to try again following an incorrect response.

In order to reflect the increasing drill down towards core beliefs that is used in traditional cognitive therapies, sessions 1 and 2 are delivered using the word ‘thoughts’ (e.g. ‘You fly to a business meeting abroad. You plan to attend the guest reception but arrive 20 min late. Upon entering the reception you look around and *think* everyone looks…’); 3 and 4 using ‘assumptions’ (e.g. ‘You are running late for an appointment and rush to get to the bus stop on time. As you approach, gesturing for the bus to wait, you see the driver look in the mirror and pull away, smiling. You *assume* that the bus driver just…’) and 5 and 6 using ‘beliefs’ (e.g. ‘You are sitting at a bus stop when a group of teenagers walk over and light up their cigarettes. As you cough loudly, they throw the empty carton saying ‘smoking kills’ towards you and laugh. You *believe* that this is…’).

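### The only model the protocol specifies for assessing efficacy is on the SRT (interpretation bias), although it names severity of paranoid symptoms as the primary efficacy outcome

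*Protocol article*

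**What the plan says.** Two sections of the protocol article speak directly to the efficacy outcome.

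- **Feasibility, double-blind randomised controlled trial.** After the main objective (feasibility), the text continues: "A secondary objective is a preliminary evaluation of efficacy". It then fixes the outcome: "For this the primary outcome is the severity of paranoid symptoms".
- **Statistical analysis.** The model is given as follows: "To assess efficacy of the intervention using the *SRT* [41] a three-factorial within-and-between group design will be used with a random-effects model". This is the only model in the section that is introduced as assessing efficacy.

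The section on secondary outcomes shows that these are different things. It separates interpretation bias, clinical symptoms and stress/distress into three domains. Of the SRT it says: "This is a standard test used to measure interpretation bias". Severity of paranoid symptoms is assigned to PANSS item 6, with three self-report scales (Paranoia Scale, Paranoid Thoughts Scale, PDI-21) alongside it. The same section promises Cohen's d with confidence intervals for each domain, described as a route to variance estimates.

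**The concern.** The article names one efficacy outcome in its objectives and ties its efficacy model to a measure from another domain. Interpretation bias is what CBM-pa sets out to change, and the description of the design calls it the hypothesised active ingredient. A difference on the SRT therefore shows first of all that the training reached its target. Whether paranoia itself improved is a separate question, and it is the one the objectives ask.

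At stake is the meaning of the trial's efficacy statement. The abstract says that a fully powered trial is warranted if the study proves feasible and gives preliminary evidence of efficacy. If the SRT moves and symptoms do not, the analysis section allows this to be called efficacy and the objectives section does not.

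**Working it through.** No figure in the plan measures this point, so the check is a comparison of the text, a count of the assessment schedule, and a check on whether the sample size is affected.

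**1. The statements side by side**

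| Section | What it fixes | Domain |
|---|---|---|
| Feasibility, double-blind RCT | Primary outcome for the efficacy objective: severity of paranoid symptoms | Clinical symptoms |
| Secondary outcomes | Paranoid symptom severity: PANSS item 6, plus three self-report scales | Clinical symptoms |
| Secondary outcomes | SRT | Interpretation bias |
| Statistical analysis | Clinically important difference: a fall of at least 20% in a symptom score | Clinical symptoms |
| Statistical analysis | Random-effects model to assess efficacy: SRT | Interpretation bias |

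The last two rows are consecutive sentences, so the analysis section is also divided within itself.

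**2. When the difference matters**

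There are four possible patterns of result. If both the SRT and symptoms improve, or neither does, the two sections lead to the same statement. If only the SRT improves, the analysis section can report efficacy and the objectives section cannot. If only symptoms improve, the reverse holds. Two of the four patterns therefore have no agreed reading.

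**3. Whether the symptom data can carry the model**

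Occasions counted from the Procedures section:

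- SRT: baseline 1 + interim 5 + week 6 (T1) 1 + follow-up 2 = 9.
- PANSS item 6: 1 + 5 + 1 + 2 = 9.
- Each of the three self-report paranoia scales: baseline 1 + T1 1 + follow-up 2 = 4.

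PANSS item 6 is scheduled at the same nine occasions as the SRT, so an arm-by-time random-effects model can be fitted to it with data already planned. The three factors of the SRT design are not named. If one of them is a feature of the SRT itself, such as sentence type (an assumption), the model does not carry over unchanged, and the symptom model needs its own short statement.

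**4. Whether the sample size is affected**

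The section on participants and study setting says that no power analysis was done for intervention outcomes. It supports the target of 60 partly by the precision of the follow-up rate: with 70% followed up, the one-sided 95% limit by the normal approximation lies 1.645 × √(0.70 × 0.30 / 60) = 0.097 from the estimate, that is 9.7 points against the stated 10. No efficacy outcome enters that figure, so moving the efficacy label to symptoms leaves 60 unchanged.

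**The case against.** **The sentence may describe only how the SRT is modelled.** The SRT has its own within-person structure, with paranoid and non-paranoid targets and foils, which could explain why its design alone is spelled out. Models for symptoms may be in an analysis plan that is not shown. This reading is possible, but the text does not state it. The point here is also not that a symptom model is absent: the article fixes a model under the label of efficacy and attaches it to something other than its named efficacy outcome.

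**Symptoms are covered elsewhere.** This stands. Cohen's d with confidence intervals is promised for clinical symptoms, dose-response is to be assessed on paranoid symptoms at each session, and the clinically important difference is a symptom change. A reader might infer that symptom effects would go unreported, or that the decision on a full trial would rest on the SRT. The documents support neither: the abstract's condition does not mention the SRT. What remains is that four paranoid symptom measures are listed and none is tied to the efficacy estimate by a model and a time point.

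**Choosing outcomes after the results is openly planned.** A reader might infer that the efficacy outcome of this trial is to be picked afterwards. The text on post-results selection concerns the primary outcome of the next trial, by Steering Group consensus, which is a proper aim of a feasibility study.

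**Task practice is largely matched.** The training and the SRT share a format. In the SRT participants "complete one of the last word’s missing letters and answer a comprehension question", and training items also use word completion and a question. A reader might infer that an SRT difference would be mere practice. However, the control items share that format, the scored part of the SRT is a similarity rating that is not among the described training responses, and foils address response bias. What stands is narrower: the control omits benign resolution of ambiguous situations, so near-transfer of that trained response to the SRT is possible without a change in paranoia.

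**Conclusion.** The mismatch is real and can be checked within the article: the efficacy objective is set on paranoid symptom severity, and the only model given for assessing efficacy is on interpretation bias. Its effect is that an SRT result without a symptom result could be reported as preliminary evidence of efficacy; nothing in the documents says that it will be.

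This should be fixed, but it does not undermine the trial. Feasibility is the primary aim, efficacy is secondary and preliminary, the plan stresses estimation over testing, symptom effect sizes will be available in any case, and the sample size is untouched. The conclusion assumes that the sentence on the SRT means what it says. If a full analysis plan already gives a lead symptom model and treats the SRT as mechanistic, only the article's wording needs to be aligned.

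**What to change.** Reconcile the objectives and the statistical analysis section before trial data are linked to the randomisation data, which the data monitoring section places after all data collection is complete.

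- State that the main preliminary efficacy estimate is the arm contrast from a random-effects (arm by time) model on one named measure of paranoid symptom severity at one named time point. PANSS item 6 at T1 is one reasonable choice; another listed paranoia scale would serve if the sponsor justifies it. Any statement of preliminary evidence of efficacy should rest on this estimate.
- Label the SRT model as the mechanism (target engagement) analysis and keep it otherwise as planned.

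The cost is one or two sentences and a little extra analysis. All the data are already scheduled, and the sample size does not change.
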